## Abstract

**Background:**

The Cardiovascular Health Awareness Program (CHAP) uses volunteers to provide cardiovascular disease (CVD) and diabetes screening in a community setting, referrals to primary care providers, and locally available programs targeting lifestyle modification. CHAP has been adapted to target older adults residing in social housing, a vulnerable segment of the population. Older adults living in social housing report poorer health status and have a higher burden of a multitude of chronic illnesses, such as CVD and diabetes. The study objective is to evaluate whether there is a reduction in unplanned CVD-related Emergency Department (ED) visits and hospital admissions among residents of social seniors’ housing buildings receiving the CHAP program for 1 year compared to residents in matched buildings not receiving the program.

**Methods/design:**

This is a pragmatic, cluster randomized controlled trial in community-based social (subsidized) housing buildings in Ontario and Quebec. All residents of 14 matched pairs (intervention/control) of apartment buildings will be included. Buildings with 50–200 apartment units with the majority of residents aged 55+ and a unique postal code are included. All individuals residing within the buildings at the start of the intervention period are included (intention to treat, open cohort). The intervention instrument consists of CHAP screens for high blood pressure using automated blood pressure monitors and for diabetes using the Canadian Diabetes Risk (CANRISK) assessment tool. Monthly drop-in sessions for screening/monitoring are held within a common area of the building. Group health education sessions are also held monthly. Reports are sent to family doctors, and attendees are encouraged to visit their family doctor. The primary outcome measure is monthly CVD-related ED visits and hospitalizations over a 1-year period post randomization. Secondary outcomes are all ED visits, hospitalizations, quality of life, cost-effectiveness, and participant experience.

**Discussion:**

It is anticipated that CVD-related ED visits and hospitalizations will decrease in the intervention buildings. Using the volunteer-led CHAP program, there is significant opportunity to improve the health of older adults in social housing.

**Trial registration:**

ClinicalTrials.gov,NCT03549845. Registered on 15 May 2018. Updated on 21 May 2019.

## Background

This study applies more than 15 years of knowledge accumulated as part of the Cardiovascular Health Awareness Program (CHAP) with the new goal of improving the cardiovascular health of seniors living in subsidized social housing in Ontario and in Quebec. Older adults living in social housing report poorer health status and have a higher burden of a multitude of chronic illnesses, such as cardiovascular disease (CVD) and diabetes, compared to seniors not living in subsidized housing [1–4].

CHAP is a community-based, patient-oriented, and interdisciplinary CVD prevention and management program. The CHAP model of community-based cardiovascular risk assessment and peer education was successfully implemented in pharmacies as a pragmatic clustered randomized controlled trial (RCT) [5] and has been shown to reduce CVD-related hospitalizations without additional costs to the healthcare system [5, 6]. A Canadian Institutes of Health Research (CIHR) team grant funded multiple pilot studies, adapting the CHAP model to other contexts, including interdisciplinary primary care clinics, places of worship, and community centers. The proposed intervention is based on the collective knowledge and best practices gained from all of these studies.

CHAP has mainly been conducted in community pharmacies, but it has been the subject of pilot projects, proof of concept studies, and RCTs in other settings as well [7–19]. Our current work revolves around building on the success of CHAP across Canada. The goal is to identify optimal conditions for scaling up and leveraging resources within communities to enable CHAP to become an ongoing initiative available to all Canadians to significantly improve community and population-based prevention and management of CVD. Although CHAP has been the subject of several studies in community pharmacies, strong clinical and policy recommendations are inevitably based on results of several high-quality RCTs conducted in different settings and populations that cumulatively have shown the benefit of the intervention in question. Therefore, a trial is needed now, to assess whether similar results can be replicated in a different context that targets a different population using a modified intervention. Based upon the promising findings from an existing community health program in subsidized housing involving specially trained paramedics, it is apparent that the CHAP model using volunteers could potentially be successful in this context [20, 21]. A full-scale RCT of the intervention is warranted. This project focuses on a more vulnerable segment of the older adult population, those living in social housing [21], compared to the typical participants in our pharmacy-based trial.

This adaptation of the CHAP program will include, for the first time, group-based educational sessions aimed at increasing cardiovascular health awareness to promote healthy habits and self-management among residents. Also, this project will assess the impact of less intense, but regular, year-round screening and monitoring sessions, which may be easier to integrate within social housing and to sustain over time.

## Methods/design

### Study aims

This study aims to determine whether there is a relative reduction in the composite outcome of unplanned *CVD-related Emergency Department (ED) or hospital admission* among residents of subsidized seniors’ housing buildings receiving the CHAP program for 1 year compared to residents in matched buildings not receiving the program.

In addition, it aims to determine:
The difference in *unplanned, all-cause healthcare utilization* (as measured by unplanned, all-cause ED visits and non-elective, all-cause hospitalization rates) among residents of subsidized housing buildings receiving the CHAP program for 1 year compared to those in matched buildings not receiving the programThe difference in *quality of life and quality-adjusted life years (QALYs)* as measured by the EuroQoL five-dimension, five-level (EQ-5D-5L) instrument in participants attending the CHAP sessions over 1 year, compared to their baseline measureThe *cost-effectiveness* of the program*Participant, volunteer, and community relations workers' experiences* regarding the programRelative changes in *risk factor measures* (such as blood pressure [BP], body mass index [BMI], and diabetes risk status) in participants attending the CHAP sessions compared to their baseline measurements.

### Study design

The trial will be an open-label, parallel, cluster RCT and is being reported according to the Standard Protocol Items: Recommendations for Interventional Trials (SPIRIT) checklist (see Additional file 1). Buildings will be the primary unit of analysis. It will be an open cohort study with repeated cross-sectional assessments comparing the outcomes of intervention and control buildings during the pre-intervention and 1-year post-intervention periods. See Fig. 1 for the study flowchart and Fig. 2 for the SPIRIT study schedule.

**Fig. 1 Fig1:**
[figure not shown]
Study design flowchart

**Fig. 2 Fig2:**
[figure not shown]
Standard Protocol Items: Recommendations for Interventional Trials (SPIRIT) figure showing schedule of interventions and assessments. *CHAP* Cardiovascular Health Awareness Program, *ED* Emergency Department, *CVD* cardiovascular disease

The trial will take place in the provinces of Ontario and Quebec, in two selected regions. Pairs (intervention-control) of subsidized seniors’ housing buildings will be selected from each province with input from local social housing provider/organization partners.

### Inclusion and exclusion criteria

Designated seniors’ buildings with 50–200 apartment units and a majority of residents aged 55 years or older will be included in the study. The buildings will have a unique postal code to be included in the sample. There are no exclusion criteria. All residents living in the building during the pre-intervention and post-intervention periods will be taken as samples for intervention and control buildings.

### Recruitment process

Recruitment of buildings will be through regions or localities in each province that have similar characteristics. Social housing organizations will be contacted and introduced to the CHAP program. Leading up to the trial implementation, presentations to managers and chief executive officers of housing organizations will be made. Previous work by the McMaster Community Paramedicine (MCP) research team has shown that it has been possible to recruit multiple social housing buildings in five separate localities across Ontario for participation in an RCT [22]; a total of 32 seniors’ housing buildings with an average of 126 apartment units each were recruited. We anticipate that we will be able to recruit the necessary number of buildings from each province (100% recruitment rate). Residents, volunteers, and housing staff of intervention buildings in each province will be recruited for four focus groups via posters and advertisements following the last CHAP session.

### Sample size

For the main outcome (ED visits and hospitalization) we computed the sample size based on the number of ambulatory care-sensitive ED visits from Canadian Institute for Health Information (CIHI) data [23]. The estimated mean number of ED visits for an individual is 0.39 (standard deviation [SD] = 0.12). We assumed that the intervention will lead to 9% difference in the mean number of ED visits by residents of intervention buildings compared to control building residents. This was based on the effect CHAP had on the hospitalization rates in the community cluster RCT [5]. We also assumed an intraclass correlation coefficient (ICC) of 0.07 for our design effect based on data analyzed from previous studies [21, 24]. Using a power of 0.8 and an alpha of 0.05, we will need a total of 1118 subsidized housing residents for each arm of the study. This is the population of approximately 12 subsidized housing buildings. We will therefore require a minimum of 12 pairs (intervention-control) of buildings; 6 pairs will be in Ontario and 6 will be in Quebec. This number is feasible based on our pre-implementation discussions with the housing providers in both provinces.

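### The 80% power rests on an individual-level SD of 0.12 that a visit count with mean 0.39 cannot have; with the plan's other inputs, power for a 9% effect is about 8–10% two-sided

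*Protocol article*

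**What the plan says.** The Sample size section of the protocol article gives the outcome's distribution per person: "The estimated mean number of ED visits for an individual is 0.39 (standard deviation [SD] = 0.12". The endpoint is named openly: "we computed the sample size based on the number of ambulatory care-sensitive ED visits from Canadian Institute for Health Information (CIHI) data". The effect is relative: "We assumed that the intervention will lead to 9% difference in the mean number of ED visits by residents of intervention buildings". Its origin is a different outcome: "This was based on the effect CHAP had on the hospitalization rates in the community cluster RCT". Clustering enters through a design effect: "We also assumed an intraclass correlation coefficient (ICC) of 0.07 for our design effect". The error rates are given as "Using a power of 0.8 and an alpha of 0.05", without saying whether the test is one- or two-sided. The result is that "we will need a total of 1118 subsidized housing residents for each arm of the study", followed by "This is the population of approximately 12 subsidized housing buildings" and a minimum of 12 pairs. The Abstract gives 14 pairs.

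The primary outcome (Study aims; Primary and secondary outcome measures) is the composite of CVD-related ED visits and CVD-related hospitalization. The Data analysis plan analyses it at building level by ANCOVA, with pair as a fixed effect and the baseline rate as covariate. The sample size takes no credit for that adjustment.

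**The concern.** A person's number of ED visits is 0, 1, 2 and so on. Such a variable cannot cluster tightly around 0.39, because nobody can have 0.39 visits. Its mean therefore sets a floor under its SD, and 0.12 is about a quarter of that floor. The floor holds for any time unit and any type of visit.

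The number of residents required is proportional to the square of the SD, so the error passes straight into the power claim. If the claim stands, a null result would be read as evidence against CHAP from a trial with 80% power for a 9% reduction, when the stated calculation does not support that power.

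**Working it through.** **Inputs.** From Sample size: mean 0.39, SD 0.12, effect 9%, ICC 0.07, power 0.8, alpha 0.05, 1118 residents and about 12 buildings per arm. From the Abstract: 14 pairs. The difference to detect is d = 0.09 × 0.39 = 0.0351. The implied building size is 1118/12 = 93.2 residents; the plan does not state it.

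**1. Reproducing 1118.** n = 2(z_α + z_β)² SD²/d², multiplied by 1 + (m − 1) × 0.07.
- One-sided 5%: n = 2 × 2.486² × 0.12²/0.0351² = 144.5, so 145. Then 1118/145 = 7.71, which is the design effect at m ≈ 97 (11.5 buildings, rounded to 12). This reproduces the plan.
- Two-sided 5%: n = 183.5, so 184. At m = 93.2 the total is 1372. Reaching 1118 needs m ≈ 73.5, or about 15 buildings, which conflicts with 12.
- At 1118 in 12 buildings with SD 0.12, power is 81% one-sided and 72% two-sided.

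So 0.12 was used as an individual SD and then inflated by a design effect of about 7.7.

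**2. The floor on the SD.** For a non-negative integer with mean 0.39, the variance is at least 0.39 × 0.61 = 0.238, reached only if nobody has more than one visit. The SD is then 0.488. Poisson gives √0.39 = 0.624. The variance ratios to 0.12² = 0.0144 are 16.5 and 27.1.

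**3. Power with the other inputs kept.** Variance of a building mean: V = SD² × [ICC + (1 − ICC)/m]; SE = √(2V/k) for k buildings per arm. One-sided power is Φ(d/SE − 1.645). Two-sided power is Φ(d/SE − 1.96) + Φ(−d/SE − 1.96). These are normal approximations; a t reference with few buildings is generally somewhat less favourable. Here m = 93.2.

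| SD | ICC | Pairs | SE | Two-sided | One-sided |
|---|---|---|---|---|---|
| 0.488 (minimum) | 0.07 | 12 | 0.056 | 10% | 15% |
| 0.488 | 0.07 | 14 | 0.052 | 10% | 17% |
| 0.624 (Poisson) | 0.07 | 12 | 0.072 | 8% | 12% |
| 0.624 | 0.07 | 14 | 0.067 | 8% | 13% |
| 0.488 | 0 | 12 | 0.021 | 40% | 52% |
| 0.488 | 0 | 14 | 0.019 | 45% | 58% |
| 0.624 | 0 | 12 | 0.026 | 26% | 38% |
| 0.624 | 0 | 14 | 0.024 | 30% | 42% |

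The ICC 0 rows stand for pairing and baseline adjustment removing all between-building variance.

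**4. What adjustment would have to achieve at ICC 0.07.** For 80% power, two-sided, 12 pairs, V may be at most (0.0351/2.80)² × 12/2 = 0.00094. At the minimum SD, V = 0.238 × (0.07 + 0.93/93.2) = 0.0190. Adjustment must explain 1 − 0.00094/0.0190 = 95%. Over 12–14 pairs, both SDs and both test conventions, the range is 93–97%.

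**5. More favourable variants** (ICC 0, 14 pairs, minimum SD).
- 126 residents per building (the average unit count of the earlier trial in Recruitment process, taking one resident per unit): 57% two-sided, 69% one-sided. Poisson: 39% and 51%.
- 93 residents, with the baseline rate also removing person-level variance at an assumed pre/post correlation of 0.3–0.5 (within-building variance × (1 − ρ²)): 49–56% and 61–68%.
- Both together, at correlation 0.5: 69% and 79%.
- 200 residents per building (the upper limit on units, at one resident per unit), no person-level gain: SE = 0.488 × √(2/2800) = 0.0130, giving 77% and 85%.

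**6. If 0.12 is the SD of building rates.** SE = 0.12 × √(2/12) = 0.049, or 0.045 for 14 pairs. Unadjusted power is 11–12% two-sided. If adjustment explained an assumed 80% or 90% of the variance, it would be 36–41% or 62–69% two-sided (48–53% or 73–79% one-sided).

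**The case against.** **The ANCOVA could rescue the power.** It will help, and the unadjusted figures should not be read as the power of the planned analysis. A reader might also take the ICC 0 rows as a hard ceiling. They are not one: the covariate is the same building's rate a year earlier in an open cohort, so residents present in both years carry some person-level variance into it, and buildings may hold more than 93 people. Working step 5 shows the gain. Of the variants computed, only one-sided testing, zero residual between-building variance, the smallest possible SD and 200 residents per building together exceed 80%. That building size does not fit the plan's equation of 1118 residents with about 12 buildings.

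**The SD may describe aggregated rates.** What 0.12 measures depends on a cited source that is not at hand. Under that reading the SD is possible, but it would already contain between-building variation. The design effect would then be misapplied, and step 6 still stays below 80%.

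**The endpoint is a disclosed proxy.** This stands. A reader might infer that the endpoint mismatch itself causes the loss of power. The document does not support that: it gives no rate for the CVD-related composite, so the effect on power cannot be computed. What remains is that the stated power is not power for the primary outcome.

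**The arithmetic is right.** It is, on a one-sided 5% test. The fault lies in an input.

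**Conclusion.** The point holds. As printed, the individual-level SD is mathematically impossible, and it is the figure that produces 1118 per arm. Correcting it to the smallest possible value, with everything else as stated and no credit for adjustment, takes power from the claimed 80% to about 10% two-sided (15–17% one-sided); Poisson gives about 8% (12–13%). At the minimum SD and ICC 0.07, the reduction detectable with 80% power two-sided is about 40% with 12 pairs (2.80 × 0.0563/0.39) and 37% with 14, not 9%.

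Three limits apply. All these figures concern the 0.39 sizing endpoint, not the CVD-related composite. Building size and sidedness are inferred because the plan states neither; even at SD 0.12, a two-sided test gives only 72%. And the finding is not that 80% power is unattainable under every conceivable assumption. It is that the stated calculation does not support it, and that at the plan's own ICC adjustment would have to explain 93–97% of the variance of building rates, which the plan does not claim.

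**What to change.** Withdraw the SD of 0.12 and the 80% power claim. Recompute power at building level for the CVD-related composite, using the pre-intervention-year administrative data already planned under Data collection. The inputs are the composite rate, its count variance given building size, and the variance left after pairing and baseline adjustment. State the sidedness of the test, the building size used, and the relative reduction detectable with the actual number of pairs. Leave enrolment unchanged, and interpret the result by its confidence interval rather than by whether it reaches significance.

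The cost is a rewritten sample-size paragraph and a less favourable stated power. It needs no extra buildings, no extra data and no change to the primary analysis.

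### Under a conventional two-sided 5% test, the stated 9% effect needs about 15 buildings per arm, so 1118 residents in 12 buildings do not give the stated 80% power

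*Protocol article*

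**What the plan says.** The Sample size section of the protocol article takes a mean of 0.39 ED visits per person with an SD of 0.12. It assumes a "9% difference in the mean number of ED visits by residents of intervention buildings" relative to control residents and an ICC of 0.07. It then concludes: "Using a power of 0.8 and an alpha of 0.05, we will need a total of 1118 subsidized housing residents for each arm". It describes this as the population of roughly 12 buildings and continues: "We will therefore require a minimum of 12 pairs (intervention-control) of buildings; 6 pairs will be in Ontario and 6 will be in Quebec".

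The Methods/design paragraph of the abstract gives the planned size: "All residents of 14 matched pairs (intervention/control) of apartment buildings will be included".

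The article does not say whether alpha is one- or two-sided. It gives no assumed number of residents per building and no absolute difference. The Data analysis plan makes the building the unit of analysis and specifies ANCOVA with pair as a fixed effect and the baseline rate as a covariate.

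**The concern.** Apart from the residents per building, which 1118/12 implies, the paragraph supplies what a standard cluster sample-size formula needs, so the result can be checked. With alpha 0.05 read in the usual way as two-sided, the formula asks for clearly more residents and buildings than the article states. Sample size, power and effect then do not fit together.

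This affects how the result is read. A null finding would be judged against a claim of 80% power for a 9% reduction. If the design delivers nearer 70% at the stated minimum, that finding is weaker evidence against a 9% effect than readers would believe. If a one-sided test was intended instead, that choice governs the primary conclusion and readers need to know it.

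**Working it through.** **Inputs (Sample size section).** Mean 0.39; SD 0.12; difference 9% of 0.39 = 0.0351; ICC 0.07; power 0.80 (z = 0.8416); alpha 0.05 (z = 1.960 two-sided, 1.645 one-sided). Residents per building m is not stated; 1118/12 = 93.2 is implied. The abstract gives 14 pairs.

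**Formulas.** Unclustered n per arm = 2(z_alpha + z_power)² SD² / d². Design effect DE = 1 + (m − 1) × 0.07. Residents per arm = n × DE.

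**Can 1118 be reproduced?**

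| Reading | n | m | DE | Residents per arm | Buildings |
|---|---|---|---|---|---|
| 9% (0.0351), two-sided | 184 | 93.2 | 7.452 | 1371 | 14.7 |
| 9% (0.0351), two-sided | 184 | 100 | 7.93 | 1459 | 14.6 |
| 9% (0.0351), one-sided | 145 | 97 | 7.72 | 1119 | 11.5 |
| 10% (0.039), two-sided | 149 | 93.2 | 7.452 | 1110 | 11.9 |
| 9% of the higher mean, 0.39/0.91 − 0.39 = 0.0386, two-sided | 152 | 93.2 | 7.452 | 1133 | 12.2 |

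For the first row, n = 2 × (1.960 + 0.8416)² × 0.0144 / 0.0351² = 183.5, rounded up to 184.

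A two-sided 9% calculation returns 1118 only if DE = 1118/184 = 6.076, so m = 1 + 5.076/0.07 = 73.5. That is 1118/73.5 = 15.2 buildings, not 12.

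**Power of 12 pairs for 9%, two-sided.** With k buildings per arm, SE = sqrt[2 × 0.0144 × (0.07 + 0.93/m)/k]. At k = 12 and m = 93.2, SE = 0.01385 and 0.0351/SE = 2.533. Normal-theory power is Φ(2.533 − 1.960) = 72%. With a noncentral t on 2 × 12 − 2 = 22 df it is 68%.

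**Larger buildings.** At k = 12, normal-theory power is 73% at m = 126 and 75% at m = 200. As m grows without limit, SE tends to sqrt(2 × 0.0144 × 0.07/12) = 0.01296, the ratio to 2.708, and power to 77%. No building size brings 12 pairs to 80% two-sided.

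**14 pairs.** At m = 93.2, SE = 0.01283 and the ratio is 2.736. Power is 78% (normal) or 75% (t on 26 df).

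**Effect detectable with 80% power at 12 pairs.** (1.960 + 0.8416) × 0.01385 = 0.0388, and 0.0388/0.39 = 9.95%, about 10% (normal approximation).

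**One-sided check.** At 12 pairs of 93, one-sided power for 9% is 81% (normal) or 79% (t on 22 df).

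**The case against.** The best defence is that two-sided testing is the reviewer's addition. The article gives only alpha 0.05, and its aims speak of a reduction. With a one-sided 5% test, every stated figure can be kept and the result is 1119 residents at about 97 per building. This stands as far as it goes: the mismatch is conditional on a two-sided test. But the article nowhere declares a one-sided test, and an unqualified alpha of 0.05 is ordinarily read as two-sided.

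A second defence is that the power figures above do not describe the planned analysis. They ignore any gain from matching and from the baseline covariate. That also stands. On the same normal approximation, a baseline correlation r leaves a variance of 1 − r², so reaching 80% needs r = sqrt[1 − (2.533/2.802)²], about 0.43, at 12 pairs. At 14 pairs it needs sqrt[1 − (2.736/2.802)²], about 0.21. The article gives no such correlation, and the fixed pair effects would cost degrees of freedom, so the net power of the ANCOVA is unknown. The article's own calculation claims none of this gain, so it cannot explain 1118.

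A third defence is that an article may leave sidedness and building size to the full protocol. Their absence alone would be no finding. The finding is that the figures printed here do not agree on the ordinary reading.

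Two stronger readings are tempting and not supported:

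- A reader might infer that 1118 comes from rounding the intervention mean to 0.35, a difference of 0.04 or 10.3%, because 141 × 7.93 = 1118.1. That match needs 141.28 rounded down and 100 residents per building, which the article does not state. At 93.2 per building, 142 × 7.452 gives 1058. Other readings in the table fit as well or better, so the source of 1118 cannot be identified.
- A reader might see 12 and 14 pairs as a contradiction. They are not: 12 is given as a minimum and 14 meets it. What is lacking is the power at 14.

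**Conclusion.** The point holds in conditional form. If the test is two-sided at 5%, 1118 residents in about 12 buildings per arm do not follow from a 9% effect, SD 0.12 and ICC 0.07. The requirement is about 1371 to 1459 residents, or 15 buildings per arm, so the stated number of residents is 18% to 23% too low (1118/1371 = 0.82; 1118/1459 = 0.77). Two-sided power for 9% is about 72% at 12 pairs (68% with t) and about 78% at the 14 pairs in the abstract (75% with t).

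These figures rest on a two-sided test, about 93 to 100 residents per building, and a simple design-effect formula without credit for matching or baseline adjustment. They take the article's SD and ICC as given. They do not show that the trial will have 70% power under its planned ANCOVA, or which slip or choice produced 1118. If a one-sided 5% test was used, the residents figure agrees with 9%, and the fault is that a choice governing the primary conclusion is not stated.

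**What to change.** Correct the Sample size paragraph so that it states the sidedness of alpha, the residents per building and the absolute difference actually used.

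- **If the test is two-sided,** keep the planned buildings and restate one of two figures. The first is the power for a 9% effect at the 14 pairs in the abstract, about 75% to 78% on the article's own inputs. The second is the effect detectable with 80% power at 12 pairs, about 10% by the normal approximation.
- **If a one-sided 5% test was used,** say so and apply it to the primary conclusion.

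In either case, give the power for the number of pairs enrolled. If credit for baseline adjustment is wanted, state the assumed correlation and allow for the degrees of freedom used by the pair effects.

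The cost is wording and a slightly less favourable stated power or detectable effect. No buildings need to be added.
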